### Methods in analysis to handle protocol non-adherence and any statistical methods to handle missing data {20c}

The primary analysis will follow a modified intention-to-treat (mITT) approach, i.e., we will not include patients who do not participate in any of the randomized treatments (drop-out between eligibility and randomization, i.e., before the start of treatment). In general, the mixed-effects model uses all post-randomization measurements of the outcome of interest to test the treatment contrast at the last follow-up time point and thus effectively accounts for missing data. Only patients without any measurement except the baseline measurement do not contribute any information to this analysis. To investigate the potential impact of missing data, different sensitivity analyses are planned. Based on findings from the pilot study—where slightly more participants in the NSSP arm failed to complete T5—we do not assume that missing data are missing completely at random (MCAR), but rather potentially missing not at random (MNAR). Thus, two complementary multiple imputation strategies will be performed as sensitivity analyses. In the first multiple imputation strategy, imputation of missing outcome values at T5 will be performed separately for each treatment arm. In the second multiple imputation strategy, missing data will be imputed together for both treatment arms. A further sensitivity analysis will be carrying forward the last available overt aggression score from earlier timepoints (e.g., T4) to estimate T5 (LOCF).

Additionally, a per-protocol analysis will be performed as a further sensitivity check. This analysis will include only those participants who attended at least 9 out of 13 group sessions and did not miss more than 2 sessions in a row. This criterion is intended to ensure that only patients with adequate exposure to the assigned intervention are included in the per-protocol analysis.

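### Potential MNAR is given as the reason for the two imputations, but no listed missing-data analysis varies that assumption

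*Protocol article*

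**What the plan says.** The section on protocol non-adherence and missing data {20c} first says that the mixed-effects model, by using all post-randomization measurements, accounts effectively for missing data. It then reports that in the pilot "slightly more participants in the NSSP arm failed to complete T5" and concludes that "we do not assume that missing data are missing completely at random (MCAR), but rather potentially missing not at random (MNAR". The next sentence draws the consequence: "Thus, two complementary multiple imputation strategies will be performed as sensitivity analyses".

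The listed missing-data analyses are:

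- In the first strategy, "imputation of missing outcome values at T5 will be performed separately for each treatment arm".
- In the second, "missing data will be imputed together for both treatment arms". The text does not say whether arm is a predictor in that model.
- A further analysis is "carrying forward the last available overt aggression score from earlier timepoints (e.g., T4) to estimate T5 (LOCF".

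A per-protocol analysis is added, defined by session attendance. No delta adjustment, reference-based imputation, pattern-mixture or selection model, or tipping point is named. The sample size section {14} expects up to 30% loss to follow-up, similar in both arms.

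**The concern.** The reasoning runs from possible MNAR to two imputations, but neither imputation, as described, departs from MAR. Each draws missing T5 values from a model fitted to observed patients and shifts nothing. The primary mixed model also relies on MAR. LOCF is not a MAR method, but it imposes one fixed assumption, no change after the last visit, and does not vary it. The per-protocol analysis concerns exposure to treatment, not missing outcomes.

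The stated reason does not point to MNAR either. A difference in T5 completion between arms argues against MCAR but is fully compatible with MAR once arm is conditioned on.

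At stake is how the robustness statement will be read. With up to 30% of T5 values missing, the primary result and the by-arm imputation, and the joint imputation too if it contains arm, could agree because they share one assumption. A reader would take that agreement as reassurance about the concern the sponsor raised.

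**Working it through.** **Inputs from the protocol article.** Sample size {14}: effect 0.55 SD, 80% power, 106 patients with individual randomization, ICC 0.075, average group size 4, loss up to 30%, 186 randomized (93 per arm). Statistical methods {20a}: two-sided 5% level.

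**The plan's own figures.** A two-sample t-test with d = 0.55 needs 52.87, so 53 per arm, or 106. Design effect: 1 + (4 − 1) × 0.075 = 1.225. Then 106 × 1.225 = 129.85, so 130, and 130 / 0.70 = 185.7, so 186. All three stated figures reproduce.

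**Effect of a departure from MAR.** If missing T5 values are worse than MAR predicts by delta (in SD), an arm's mean moves by missing fraction × delta. Effects are given as MAAP benefit.

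| Missing MAAP / NSSP | Delta MAAP / NSSP | Contrast |
|---|---|---|
| 30% / 30% | 0.2 / 0 | 0.55 − 0.30 × 0.2 = 0.49 |
| 30% / 30% | 0.5 / 0 | 0.55 − 0.30 × 0.5 = 0.40 |
| 30% / 30% | 0.8 / 0 | 0.55 − 0.30 × 0.8 = 0.31 |
| 30% / 30% | 0.5 / 0.5 | 0.55 − 0.15 + 0.15 = 0.55 |
| 25% / 35% | 0.5 / 0.5 | 0.55 − 0.125 + 0.175 = 0.60 |

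The deltas and the 25% / 35% split are assumptions.

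**Approximate significance limit.** With 65 analysed per arm: 1.96 × √1.225 × √(2/65) = 0.38. The MAAP-only shift that takes 0.55 to this limit is (0.55 − 0.38) / 0.30 = 0.57 SD. The limit ignores precision gained from baseline and earlier visits.

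**The joint imputation, arm omitted.** Imputed values then carry the arm difference only through their predictors. If b is the share carried, the contrast is 0.55 × (0.70 + 0.30 × b), even under MCAR.

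- Baseline as the only predictor: b = 0, giving 0.70 × 0.55 = 0.385 (simulated 0.38).
- Baseline and T1, assumed within-patient correlation 0.3 to 0.6: b about 0.29 to 0.44, giving about 0.43 to 0.46 (simulation agrees).
- T4 as predictor, assumed R² 0.2, 0.4, 0.6: b about 0.49, 0.66, 0.79, giving about 0.47, 0.49, 0.52.

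**The joint imputation, arm included.** Under MCAR it gives 0.55, as does the by-arm imputation.

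**Would the planned analyses reveal MNAR?** A simulation with 93 per arm and true effect 0.55 let MAAP patients with worse T5 scores drop out more often (logistic slope 1 per SD, about 27% missing), with 30% missing at random in NSSP. It assumed correlations of 0.3 to 0.6, a constant effect from T1 to T5, independent patients, T1 and baseline as imputation predictors, and a random last visit for LOCF.

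| Analysis | Mean estimate (truth 0.55) |
|---|---|
| Complete cases | 0.70–0.76 |
| Imputation by arm | 0.69–0.76 |
| Joint imputation with arm | 0.68–0.75 |
| LOCF | 0.62–0.67 |
| Joint imputation without arm | 0.50–0.58 |

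With arm modelled, both imputations largely repeat the complete-case bias. Without arm, the joint imputation lands near the truth only because its attenuation offsets that bias. The primary mixed model was not simulated.

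**The case against.** The strongest reply has four parts.

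**Scope.** Imputation predictors and delta grids usually belong in the SAP, which is not shown. That holds for the predictors, so the silence about arm is a point to clarify, not an error. It does not hold for the main point: the article itself lists the methods and presents them as the answer to possible MNAR, and an SAP that implemented this list faithfully would inherit the gap.

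**Dilution.** A reader might infer that the joint imputation dilutes the effect by its nature. The text does not support this; it happens only if arm is left out. In that case it would also be wrong to say that no planned analysis could reveal a departure, because the joint imputation would visibly disagree with the by-arm one. It is then an unlabelled conservative scenario. Reference-based imputation, with MAAP dropouts following NSSP, can give the same 0.385 when no post-baseline score is used, so attenuation as such is not a fault. What is missing is a stated assumption and a way to vary it.

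**Asymmetry.** A reader might take the drop from 0.55 to 0.40, which is 0.15 / 0.55 = 27%, as the expected bias. Nothing in the documents supports a MAAP-only departure: {14} expects similar dropout, {20c} reports slightly more T5 loss in NSSP, and equal shifts leave the contrast unchanged or, with more NSSP loss, raise it. The figure is one scenario.

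**Mitigation.** The retention section {18b} provides for assessment after stopping therapy, flexible or remote visits and tiered reimbursement; assessors are blinded {17a}; and LOCF from T4 would bridge only four weeks. All of this stands and lowers the risk. That dropouts are mainly patients relapsing into aggression is not stated anywhere; the discussion names personal, logistical or psychological reasons.

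**Conclusion.** The concern holds in a limited form. Section {20c} justifies its imputations by possible MNAR, yet no listed analysis contains a parameter that moves away from MAR, and LOCF substitutes one fixed assumption for another. The cited pilot imbalance excludes MCAR at most.

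The size depends on assumptions. With 30% missing, the T5 contrast changes by 0.30 SD for each SD by which the arms' departures differ, so a difference of about 0.57 SD to the disadvantage of MAAP takes the planned effect to the approximate significance limit, while equal departures with equal dropout do no harm. The joint imputation either attenuates 0.55 to about 0.38 with baseline only, or to about 0.43–0.52 with a post-treatment score (arm omitted), or adds little to the by-arm imputation (arm included). These are illustrations, not forecasts for this trial.

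The primary analysis and the sample size are not called into question. What is unsupported is any claim that the listed analyses test robustness to MNAR.

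**What to change.** - Keep the by-arm imputation as the MAR reference.
- Add delta-adjusted multiple imputation with a tipping-point grid, for example 0 to 1 SD added to imputed T5 scores, varied separately in each arm so that unequal and equal departures are both covered. A reference-based imputation, with MAAP dropouts following the NSSP distribution, is an optional addition.
- If the joint imputation is kept, either include arm in its model or label it as a deliberately conservative scenario.
- Reword {20c} so that neither multiple imputation nor LOCF is presented as addressing MNAR, and so that the difference in pilot completion is cited against MCAR only.
- State that the T5 conclusion is called robust only up to the reported tipping point.

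The cost is wording, some programming and one more table; no new data are needed. Last patient out is planned for November 2026, so the analysis can still be prespecified. The downside is a possibly less favourable robustness statement.

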### Plans to give access to the full protocol, participant level-data and statistical code {31c}

Due to the use of privacy sensitive information, the database will not be made available in a public repository. Anonymized participant-level data may be shared on reasonable request, e.g. for meta-analysis. The statistical code associated with peer-reviewed publications resulting from this study will be made available to the public.

## Oversight and monitoring

### Composition of the coordinating center and trial steering committee {5d}

This multicenter study was designed at the University Hospital of Heidelberg, Germany, and conducted at sites in Aachen, Berlin, Bielefeld, Bonn, Frankfurt, Heidelberg, and Munich. The coordinating center at the University Hospital Heidelberg is responsible for the overall management and organization of the study. Day-to-day support is provided by the sponsor/chief principal investigator, who maintains oversight of the trial, and the central study coordinator, who ensures the day-to-day administration and execution of the study protocol. This includes coordinating recruitment, data collection, and communication with and between sites.

The central study coordinator ensures that all trial-related tasks are in accordance with the protocol and that site-specific issues are addressed in a timely manner. Each participating site has one or two principal investigators, a study site coordinator, and additional dedicated study staff—including study therapists, diagnosticians, and research assistants—who play a key role in the conduct and day-to-day support of the trial.

The site study coordinators are responsible for the local execution of the study protocol, for patients’ safety and report of (serious) adverse events, overseeing activities such as patient recruitment, diagnostic assessments, treatment allocation, treatment delivery, follow-up visits, and other site-specific trial operations. Regular meetings are held both at the site level and across sites to maintain oversight, ensure protocol adherence, monitor safety, and support the achievement of study objectives.

Specifically, the project coordinators meet monthly to discuss trial progress, address protocol-related questions, and review recruitment, retention, and data quality across centers. The diagnosticians meet on a quarterly basis to ensure consistency in diagnostic procedures across sites, address assessment-related questions, and discuss any diagnostic challenges that may arise. In addition, all participating sites—including the principal investigators and the chief investigator—convene quarterly to review overall study progress, ensure protocol adherence, discuss site-specific developments, and coordinate cross-site collaboration and oversight.

### Composition of the data monitoring committee, its role and reporting structure {21a}

This trial has a Data Safety Monitoring Board (DSMB), an independent group of experts in psychiatry, clinical research, and patient safety who are responsible for ensuring patient safety throughout the trial. The primary responsibility of the DSMB is to ensure that the trial is conducted in accordance with the protocol, applicable regulatory requirements, and ethical guidelines, and that the safety of the participants is protected. The DSMB monitors (serious) adverse events (AEs and SAEs) and ensures that the trial is conducted according to safety standards. It provides strategic guidance on the progress of the trial, addresses any issues that arise during the trial, and makes recommendations for adjustments as necessary. The DSMB meets semi-annually with the sponsor and the central study coordinator to review safety data and recruitment and to make recommendations. In addition, the KKS provides data management support for this trial and oversees the scientific and ethical integrity of the trial. KKS monitoring is conducted at study initiation and annually at each participating site to ensure that the trial is following the protocol and regulatory requirements and to review progress, data safety and any emerging concerns.

### Adverse event reporting and harms {22}

There are no direct risks to patients participating in this study. All patients and one of the two group therapists fill out a participation-related documentation after each therapy session, including questions about acute suicidality. Patients also have the option of a brief crisis intervention with one of the two group therapists. Potential SAEs are defined as patient death, acute mental illness requiring hospitalization, acute suicidality, and acute aggression. Potential AEs are defined as delinquency or threat of violence, serious physical illness, serious accident, and new-onset acute mental disorder (comorbid with borderline personality disorder). The study collects, assesses, and manages AEs and SAEs, as well as any unintended effects related to the study interventions or their administration. AEs and SAEs are recorded; SAEs are reported to the chief principal investigator within 24 h, and then reported to the DSMB. To this end, the occurrence of SAEs is categorized, and their severity, relationship to study interventions, and outcome are systematically assessed and documented in the eCRF. Appropriate follow-up actions will be taken for all SAEs in consultation with the DSMB. The DSMB will advise whether the trial should be continued or stopped if a cluster of SAEs is suspected. These decisions will be based on ongoing risk assessments and careful evaluation of the available safety data. Periodic reviews are performed and results are reported to the ethics committees as required.

Any patient showing signs of acute suicidality or severe aggression requiring immediate crisis intervention will be referred to specialized facilities while continuing their randomized treatment, provided that the crisis intervention does not exceed 14 days. In cases of violence, either during therapy sessions or in life-threatening circumstances outside of therapy, therapy will be discontinued and the participant will be referred to appropriate care, either inpatient or outpatient.

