### Frequency and plans for auditing trial conduct {23}

In accordance with Good Clinical Practice (GCP) standards, trial conduct is subject to multiple levels of monitoring and oversight to ensure compliance with the protocol, regulatory requirements, and ethical guidelines. The Trial Steering Committee and the DSMB (representing the independent Data Monitoring Committee) convene every six months to evaluate the overall conduct of the trial, review accumulated data, and monitor for any potential safety or protocol adherence issues. In addition, independent monitoring is conducted annually by the KKS. These audits are performed in accordance with ICH-GCP guidelines and the KKS Standard Operating Procedures (SOPs). The KKS conducts on-site visits once per year at each site, with the option for remote video monitoring if needed. These audits cover documentation of informed consent, participant data, administration of interventions, and reporting of (S)AEs. All monitoring reports are subject to quality control by the KKS and are forwarded to the coordinating site for review and, if necessary, action. Given the low-risk nature of the intervention, no additional ethics committee meetings are conducted beyond the initial ethics approval and oversight provided by the institutional review boards. The combination of DSMB oversight and KKS monitoring ensures that participant safety, data integrity, and regulatory compliance are maintained throughout the trial.

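### Serious accidents and serious physical illnesses are listed as AEs, so non-fatal cases, even hospitalised ones, fall outside the prompt reporting steps stated only for SAEs

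*Protocol article*

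**What the plan says.** Section {22} of the protocol article sets out two lists. For serious events: "Potential SAEs are defined as patient death, acute mental illness requiring hospitalization, acute suicidality, and acute aggression". For other events: "Potential AEs are defined as delinquency or threat of violence, serious physical illness, serious accident, and new-onset acute mental disorder".

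It then gives the handling: "AEs and SAEs are recorded; SAEs are reported to the chief principal investigator within 24 h, and then reported to the DSMB". The next step also names SAEs only: "To this end, the occurrence of SAEs is categorized, and their severity, relationship to study interventions, and outcome are systematically assessed". The same section puts follow-up of SAEs in consultation with the DSMB, and ties the board's advice on the trial's future to SAEs: "The DSMB will advise whether the trial should be continued or stopped if a cluster of SAEs is suspected".

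The section on the data monitoring committee {21a} is wider: "The DSMB monitors (serious) adverse events (AEs and SAEs", with meetings twice a year at which safety data are reviewed. Section {23} repeats the six-monthly rhythm. Criteria for discontinuing or modifying allocated interventions {11b} makes an SAE one of the grounds on which allocated treatment may end.

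**The concern.** The protocol calls two kinds of event serious and then files them in the category that is not SAE. It also uses different logic for body and mind. For mental illness, a consequence (admission to hospital) makes the event an SAE. For physical illness and accidents no consequence short of death does so.

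The label matters because the faster and more structured safety steps are attached to it. A run of hospitalised accidents or illnesses in one arm would not, on the text, start the prompt reporting chain or count towards a suspected SAE cluster. That weakens oversight of participants while the trial is running. It also means that the lists of AEs and SAEs by arm planned in section {20b} would separate events of similar consequence according to their cause.

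**Working it through.** No sample size, power or event figure underlies this point, so there is no plan figure to reproduce. The check is a comparison of the text in sections {22} and {21a}, followed through for one test case.

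**Step 1. Test case.** A participant is admitted to hospital after a non-fatal accident. Against the four SAE items:

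- Death: no.
- Acute mental illness requiring hospitalisation: no, because the cause is not mental illness.
- Acute suicidality: no.
- Acute aggression: no.

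Against the AE list, serious accident matches. The result is the same for a hospitalised, non-fatal physical illness, which matches serious physical illness on the AE list. A fatal accident or illness is an SAE through the death item.

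**Step 2. What follows from each label.**

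| Step | SAE | AE |
|---|---|---|
| Recorded | yes | yes |
| Collected, assessed and managed in general terms | yes | yes |
| Report to chief principal investigator | within 24 h | no deadline stated |
| Event-level report to the DSMB | yes, no deadline stated | not stated |
| Systematic record of severity, relatedness and outcome | yes | not stated |
| Follow-up in consultation with the DSMB | yes | not stated |
| Counts towards a suspected cluster prompting continue/stop advice | yes | not stated |
| Periodic DSMB review | semi-annual | semi-annual |

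**Step 3. Timing.** With two DSMB meetings a year, the interval is 12 / 2 = 6 months. An event that occurs just after one meeting and is seen only at the next waits up to about 6 months. The 24-hour limit is a different clock: it runs to the chief principal investigator, and the onward step to the DSMB has no stated deadline. The two figures therefore cannot be subtracted to give a delay. What the text supports is that an SAE has a 24-hour start to its route and an AE has no stated deadline at all.

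**Step 4. Link to treatment.** Section {11b} lists discontinuation due to an SAE among its criteria and introduces its examples as included items, not as a complete set. Widening the SAE category without comment could therefore be read as widening that criterion too.

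**The case against.** The strongest reply is that this is a condensed article. Both lists are headed as potential events, neither is said to be exhaustive, and the full protocol, monitoring manual and eCRF are not shown. A general definition of seriousness may sit there. That is fair as far as omissions go, but this is not an omission. The article expressly places these two kinds of event among AEs, and a general definition elsewhere would conflict with that sentence and still need reconciling.

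Several stronger readings are tempting, and the article does not support them:

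- **That these events never reach the DSMB.** Section {21a} puts AEs within the board's remit and lets it address any issue that arises. What is missing is prompt, event-level notice.
- **That the delay grows from 24 hours to six months.** This mixes the investigator's clock with the board's meeting interval. Section {5d} also provides monthly coordinator meetings and quarterly meetings of all sites with the chief investigator. These could bring an event to the sponsor sooner, although they carry no event deadline and are not DSMB reports.
- **That SAE counts by arm will certainly be wrong.** No event data are given, and AEs would still be listed by arm.
- **That accidents may be hidden self-harm or violence.** Nothing in the article says so.
- **That the commitment to GCP in section {23} is breached.** The sentence beginning "In accordance with Good Clinical Practice (GCP) standards" concerns monitoring and oversight of conduct, not event definitions.
- **That the line between acute aggression and threat of violence is a defect of the same kind.** The article gives no recording criterion for it, but such detail is commonly left to the full protocol or the eCRF.

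The objection that redefining SAEs could change a treatment rule stands, and it limits the form of the remedy.

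**Conclusion.** The point holds in a limited form. On the article's own wording, a non-fatal serious accident or physical illness, even one requiring admission, lies outside the 24-hour report, the event-level DSMB report, the systematic documentation and the cluster trigger. Its only stated DSMB exposure is the semi-annual review, so the board may first see it up to about six months after it occurs.

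This assumes that sites apply the two lists as printed and that no fuller definition overrides them. The number of events affected is unknown. The primary and secondary efficacy analyses are untouched. It is a safety-reporting weakness that should be corrected, and the trial is described as ongoing, with last patient out planned for November 2026.

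**What to change.** Reconcile the two lists in section {22}. For reporting and coding, let physical illnesses and accidents that are serious by consequence enter the SAE stream. Hospitalisation, already used for mental illness, is the obvious consequence to carry across. Re-code events already recorded under the same rule, so that the lists by arm rest on one definition throughout.

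State in the amendment that the change concerns reporting and coding only. Reconcile it explicitly with section {11b}, so that the present criterion for ending allocated treatment is neither widened nor narrowed by the new coding.

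The cost is a short protocol and eCRF amendment, for which the amendments section {25} already gives a route, a one-off re-coding exercise, and modestly more SAE reports for the sites, the chief principal investigator and the DSMB to handle.
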